### Participating centres

The lead investigator (an experienced researcher and a cardiologist at the French National Cardiac Amyloidosis Reference Centre) identified 34 hospitals and invited them to participate in the HEAR; all accepted (Appendix A and Fig. 1). The 34 participating centres are representative of France’s geographic and ethnic diversity. Each centre has been asked to register consecutive patients. The distribution of patient inclusions by centre as of March 1^st^, 2024, is shown in Fig. 2. Four centres had not started recruitment at that date. Lastly, it should be noted that we intend to extend the HEAR to other European countries.

**Fig. 1 Fig1:**
[figure not shown]
A map showing the participating centres in France

**Fig. 2 Fig2:**
[figure not shown]
The numbers of patients included at each centre (as of March 1^st^, 2024)

### Definition, inclusion, and exclusion criteria

We apply the diagnostic criteria for CA given in the European Society of Cardiology’s 2021 expert consensus [17]. The criteria for patient inclusion in the HEAR are as follows: age 18 or over, referral for suspected CA or a confirmed diagnosis of CA, and coverage by the French social security system. The main exclusion criterion was refusal to participate in the registry. Patients included in the HEAR do not receive any financial compensation.

### Study tools

Clinical data are collected using an e-CRF that can be accessed over the Internet by the participating physicians and the clinical study coordinator. Data related to the centre and the details of each participating physician (family name, first name, postal address, e-mail addresses, telephone number, fax numbers, age, sex, medical specialty, and department) are collected via another e-CRF.

The patient-related data collected for the HEAR include demographic variables (date of birth, sex, country of origin, and lifestyle) and medical variables (medical history, symptoms, clinical, laboratory and imaging data, treatments, and genetic test results for cardiomyopathies).

### Longitudinal follow-up

Given that the study is observational, patients will be followed up according to each centre’s standard procedures; the patient’s management will not be modified and no additional visits will be required. However, vital status and clinically significant events will be collected for all patients included in the HEAR RETROSPECTIVE cohort. In the absence of a visit to the centre or inclusion in the HEAR PROSPECTIVE cohort (see below), the vital status (alive or dead) of patients will be confirmed successively by (i) consulting the centre’s appointment scheduling software, (ii) phoning the patient or a relative if the patient had not attended the participating centre after the study set-up, (iii) contacting the patient’s general practitioner by phone or by post, and (iv) contacting the town hall corresponding to the patient’s last known address by phone or by post.

For all patients included in the HEAR PROSPECTIVE cohort, vital status (alive or dead) will be checked annually. If a year goes by without the collection of data (i.e. failure to visit the study centre), the investigators will seek to document vital status and events that occurred in the previous year by carrying out the procedures described above for the HEAR RETROSPECTIVE cohort.

In accordance with the current French legislation and regulations, adverse events (whether serious or not) will be notified to the competent authorities by the study investigators. These events will be recorded by the investigators throughout the study, using the dedicated sections of the e-CRF.

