### Design and sampling

The HEAR is a French, multicentre, observational registry for patients with suspected or confirmed CA. We expect to include 8,500 patients between July 2021 and December 2027. The registry will comprise retrospective, retroprospective and prospective cohorts.

Firstly, the HEAR RETROSPECTIVE cohort will comprise deceased patients with confirmed diagnosis of CA, who met the inclusion criteria and were treated at the centre after 2009. The data from this cohort will enable us to characterize the natural history of the disease.

Secondly, the HEAR RETROPROSPECTIVE cohort will comprise live patients with a confirmed diagnosis of CA and real-life follow-up from the date of inclusion, who have been treated after 2009 and are still being monitored at the centre. The patients will be asked to give their written, informed consent for the retroprospective and prospective collection of their personal data.

Thirdly, the HEAR PROSPECTIVE cohort will comprise patients referred to the participating centres for suspected CA. The real-life data from this cohort will enable us to characterize (i) diagnostic pathways for patients with suspected amyloidosis and (ii) changes in the management of CA. The patients will be asked to give their written, informed consent for the prospective collection of their personal data.

We are collecting demographic, clinical, laboratory, imaging, and QoL data (via the systematic completion of the AmyloAFFECT-QOL questionnaire, the MLHFQ and the KCCQ) and diagnostic data at baseline for all registered patients, by using a structured electronic case report form (e-CRF)). We will also collect data on patient management by the cardiologists and specific details of treatments. Lastly, we intend to collect in-hospital data on outcomes (deaths, cause of death, and hospital readmissions) annually.

Furthermore, the HEAR will include a digital health component through the development of an artificial-intelligence-powered patient chatbot designed to (i) provide educational support and personalized guidance, (ii) explain quality-of-life questionnaires in accessible terms, (iii) facilitate the completion of patient-reported outcome measures (PROMs), (iv) collect patient-reported experience measures), and (v) promote health literacy and patient empowerment.

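### Vital-status tracing is assigned to a cohort defined as deceased, and the living confirmed (RETROPROSPECTIVE) cohort has no explicitly assigned annual check

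*Protocol article*

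**What the plan says.** Design and sampling (protocol article, Methods) sets up three cohorts:

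- RETROSPECTIVE: "the HEAR RETROSPECTIVE cohort will comprise deceased patients with confirmed diagnosis of CA".
- RETROPROSPECTIVE: "live patients with a confirmed diagnosis of CA and real-life follow-up from the date of inclusion".
- PROSPECTIVE: "the HEAR PROSPECTIVE cohort will comprise patients referred to the participating centres for suspected CA".

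Longitudinal follow-up then gives the follow-up rules. It says that "vital status and clinically significant events will be collected for all patients included in the HEAR RETROSPECTIVE cohort". The next sentence, which lists the tracing steps, opens: "In the absence of a visit to the centre or inclusion in the HEAR PROSPECTIVE cohort (see below), the vital status (alive or dead". The steps are taken in order: the centre's scheduling software, a telephone call, the general practitioner, and the town hall of the last known address. The telephone step reads "phoning the patient or a relative if the patient had not attended the participating centre after the study set-up".

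The following paragraph gives the yearly rule: "For all patients included in the HEAR PROSPECTIVE cohort, vital status (alive or dead) will be checked annually". If a year passes without data on a PROSPECTIVE patient, investigators look for vital status and events in that year. They do so by the steps above, which this paragraph describes as those of the RETROSPECTIVE cohort.

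**The concern.** The follow-up rules do not fit the cohort definitions. A cohort made up of deceased patients needs no alive-or-dead tracing, and nobody in it can be telephoned. The cohort that does need tracing, living patients with confirmed disease, is not named in the section.

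The RETROPROSPECTIVE cohort supplies the continuing outcomes of confirmed patients treated after 2009 who are still alive. Secondary objectives (vi) to (viii) cover prognosis and its change over time, treatments with their benefits and side effects, and hospital admissions and interventions. The Discussion also presents the registry as a platform for survival comparisons, citing one made before and after tafamidis became available. Such analyses need deaths to be found equally completely, and on the same timetable, in the cohorts that are pooled or compared. If one living cohort is checked every year and the other on no stated schedule, a difference in observed survival may partly reflect how hard each centre looked.

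**Working it through.** No arithmetic applies: the document states no figure on this point and gives no rates from which to derive one. The check sets the definitions against the rules.

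**Step 1. Rule against definition, by cohort.**

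| Cohort | Status by definition | Tracing steps | Annual vital-status check | Missed-year search for status and events |
|---|---|---|---|---|
| RETROSPECTIVE | Deceased, confirmed | Assigned by name | Not needed | Not needed |
| RETROPROSPECTIVE | Living, confirmed | Not named | Not named | Not named |
| PROSPECTIVE | Referred on suspicion | By cross-reference | Assigned by name | Assigned by name |

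The first row contradicts itself: vital status is already known for everyone in that cohort. The second row is empty where the definitions call for an entry.

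**Step 2. Could the tracing sentence cover the RETROPROSPECTIVE cohort anyway?** Partly. It speaks of patients without a visit or without inclusion in the PROSPECTIVE cohort, and a living confirmed patient who stops attending can meet that condition. Three limits remain:

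- It sets no interval.
- It confirms vital status only. The collection of events is in the sentence before, which names the RETROSPECTIVE cohort.
- The telephone step is conditional on no attendance since study set-up. Read literally, it does not apply to a patient who came once after set-up and then stopped. That suits a single check at the start better than repeated follow-up.

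**Step 3. Do other sections supply a yearly check?**

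- Design and sampling plans annual collection of deaths, causes of death and readmissions with no cohort restriction, but as in-hospital data. By itself this does not capture deaths elsewhere.
- Collection of the data says that patient status is monitored regularly, without an interval, and that investigators are invited to contact patients lost to follow-up. Neither is limited to one cohort. The second is an invitation, with no schedule and no link to the general practitioner and town-hall steps.

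**Step 4. What follows.** RETROPROSPECTIVE patients have several possible routes to ascertainment. None is both yearly and able to find deaths outside hospital. The PROSPECTIVE cohort has a rule that is both.

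**Step 5. Direction of any bias.** Suppose that patients who stop attending are not traced, are censored at their last visit, and die at a higher rate than those who still attend. Survival is then overstated, and deaths and admissions are undercounted. If mortality is the same after stopping, the survival estimate is not biased. The document gives no information on any of these conditions.

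**The case against.** The strongest reply is that this is a slip of labels and that no procedure is missing. Telephoning a previously treated patient makes sense only if that patient may be alive, so the section probably uses RETROSPECTIVE loosely for all previously confirmed patients. On that reading both tracing and event collection already cover the living ones. RETROPROSPECTIVE patients also consent to prospective data collection, so they may be meant to pass into PROSPECTIVE follow-up. Finally, a condensed article may leave schedules to the full protocol, and tracing carried out once before analysis would recover deaths whether or not it was done yearly.

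Much of this stands. The label slip is plausible, and the lack of an interval is not in itself a bias. But the loose reading still leaves the living confirmed cohort without the yearly check. The second reading is not stated, and it sits badly with a PROSPECTIVE cohort defined by referral on suspicion. Nor is this only omitted detail: the article does print a rule for each of two cohorts, and one of those rules is attached to patients to whom it cannot apply.

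A reader might go further and infer that deaths after patients stop attending are missed, or try to put a number on the loss. The document does not support either. The provisions in steps 2 and 3 can each reach these patients. Any number would need assumed rates for mortality among attenders, for stopping, and for mortality after stopping, and would have to suppose no tracing at all and censoring at the last visit. The first supposition conflicts with the text. The second is an analysis rule that the article does not state.

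**Conclusion.** The cohort labels in Design and sampling and in Longitudinal follow-up cannot both be right as written. The living confirmed cohort has no explicitly assigned annual vital-status check or missed-year search. That much rests on the text alone and is firm.

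The consequence is a risk: deaths in this cohort may be ascertained incompletely, or at different times than in the PROSPECTIVE cohort, and this could affect the results for objectives (vi) to (viii). Any bias depends on how centres trace these patients in practice, on whether those who stop attending have a different prognosis, and on how they are censored. Its size cannot be estimated from the document.

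**What to change.** In Longitudinal follow-up:

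1. State that the tracing steps apply to RETROPROSPECTIVE patients. For the RETROSPECTIVE cohort, state that the date and cause of death and the clinical events are taken from the records.
2. Reword the annual rule so that it names both the RETROPROSPECTIVE and the PROSPECTIVE cohorts, with the same missed-year search for vital status and events in each, and correct the cross-reference to the tracing steps accordingly.
3. Run one catch-up status check on RETROPROSPECTIVE patients already included before any survival analysis.

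The cost is a change of wording, the single catch-up, and a yearly status check for RETROPROSPECTIVE patients without a visit. The procedure already exists for the PROSPECTIVE cohort. No extra visit, examination or change in care is needed. Inclusion is planned to run to December 2027, so the correction can still take effect during the registry.

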### Collection of the data

The data will be entered in the e-CRF directly by the investigating physicians. Consistency tests will be run on the study database, in order to check the consistency of dates (given the timeline of events) and the most important major variables. These checks will be defined in a data validation plan validated by the study sponsor (Heart’s Foundation).

The data’s completeness and quality and the level of compliance with study procedures will be checked regularly throughout the study.

Patient inclusions and status will be monitored on a regular basis by the study’s clinical research associates. Investigators will be invited to contact any patients lost to follow-up.

The principal investigator will use a specific remote access to check that the e-CRF is completed correctly with regard to data completeness and quality. The clinical study coordinator will also be in charge of sending the participating physicians data queries generated by the consistency tests and ensuring that the queries are answered in full. To this end, regular telephone interviews between the clinical study coordinator and the investigators will be help the latter to fill in and correct (if required) the data.

The investigating physicians have authorized the sponsor or any person authorized by the sponsor to carry out on-site audits (during or at the end of the study), in order to check that the study is being conducted in accordance with the approved protocol. The competent authorities may order an inspection. The investigators must guarantee the quality and authenticity of the data collected and compliance with ethical principles.

### Data collection category

The comprehensive set of variables collected within the HEAR database have been structured to ensure robust, standardized, and longitudinal data collection aligned with international clinical research standards (Table 2). Each variable falls under a defined data category and is associated with specific time points of collection (such as screening, follow-up, or both), in order to capture the dynamic nature of disease progression, therapeutic intervention, and patient outcomes. The registry includes critical domains such as patient demographics, the amyloidosis subtype, genetic characterization, detailed general and cardiological medical histories, specific symptoms related to amyloidosis, and therapeutic regimens. Furthermore, the registry includes vital signs, biomarker data, multimodal cardiac imaging (e.g., echocardiography, MRI, and scintigraphy), biopsy findings, and adverse event reports. Importantly, patient-reported outcomes (e.g. QoL) are collected as a guide to the impact of the disease and treatments on daily living. This structured, exhaustive data framework is essential for enabling longitudinal analyses, fostering translational research, and supporting real-world evidence generation in the field of CA.

**Table 2 Tab2:** Variables collected in the HEAR database

Data category	Examples of collected variables	Time of collection	Comments
Informed consent	Date, version of consent form	Screening	ICH-GCP compliant
Demographics	Age, sex, weight, height	Screening	Baseline characteristics
Cardiomyopathy	Cardiac amyloidosis (ATTRv, ATTRwt, AL), ATTRv asymptomatic, AA, ApoA1, ApoA2, ApoA3, ApoA4, Other cardiomyopathy	Screening	
Type of mutation	Cardiac genotype, neurologic genotype, mixed genetic	Screening	
General medical history	Family history, allergies, comorbidities (AHT, diabetes, dyslipidaemia)	Screening	Baseline characteristics
Cardiac medical history	Heart failure, Cardiac Valvular disease, Cardiac Arrhythmia, Cardiac Device	Screening	Baseline characteristics
Amyloidosis-specific medication	ATTR (tafamidis, patisiran, vutrisiran, and inotersen) and AL (chemotherapy): dosing regimen, start date, stop date	Screening + follow-up	
Concomitant medication	Drug name, dosing regimen, duration	Screening + follow-up	Potential interaction with treatment
Symptoms	First cardiac and extracardiac symptoms, deafness, orthostatic hypotension, dysautonomia, carpal tunnel syndrome, neuropathy, Dupuytren contracture, lumbar canal, hip prosthesis, knee prosthesis	Screening + follow-up	
Vital signs	NYHA, Blood pressure, heart rate	Screening + follow-up visits	
Laboratory data	NT-proBNP, BNP, troponin T, troponin I creatinine, GFR, liver enzyme, albumin, prealbumin, lipid panel, iron panel, interleukin-6, calprotectin (MRP8/14),	Screening + follow-up visits	
Electrocardiogram data	Heart rate, rhythm, QRS interval, PR interval	Screening + follow-up visits	
Echocardiography data	IVS, LVEF, LV global strain, TAPSE, PASP, E/A, E/E’	Screening + follow-up visits	
Tissue biopsy	Salivary gland, cardiac biopsy, carpal tunnel biopsy, nerve biopsy,	Screening + follow-up (if needed)	
MRI	LVEF, T1, T2, ECV	Screening + follow-up (if needed)	
Scintigraphy	HMDP/DPD/PYP. Late phase visual scoring, H/CL lung ratio. Early phase: heart-to-mediastinum ratio	Screening + follow-up (if needed)	
Medication	All treatments and changes	Baseline and follow-up	Amyloidosis treatment and others
Cardiac adverse events and vital status and cause of death	Type, severity, relationship with treatment (heart failure, valve failure, thromboembolic event, coronary event, conduction event, arrhythmia event, other cardiac event	Follow-up	Reported in accordance with GCP
Extracardiac adverse events	Infectious event, dialysis, haemorrhagic event, other extracardiac event.	Follow-up	
Quality of life questionnaire	AmyloAFFECT-QoL, MLHFQ, KCCQ	Screening + follow-up	

ICH-GCP: International Council for Harmonisation - Good Clinical Practice; ATTRv: Transthyretin amyloidosis, variant (hereditary); ATTRwt: Transthyretin amyloidosis, wild-type; AL: Light chain amyloidosis; AA: Serum amyloid A amyloidosis; Apo: Apoprotein; AHT: Arterial hypertension;, NYHA: New York Heart Association; NT-proBNP: N-terminal B-type natriuretic peptide; BNP: B-type natriuretic peptide; GFR: Glomerular filtration rate; IVS: Interventricular septum; LVEF: Left ventricular ejection fraction; TAPSE: Tricuspid annular plane systolic excursion; PASP: Pulmonary artery systolic pressure; ECV: Extracellular volume; HMDP: Hydroxymethylene diphosphonate; DPD: Diphosphonopropanodicarboxylic acid; PYP: Pyrophosphate; HCL: Heart-to-contralateral-lung; QoL: Quality of life; MLHFQ: Minnesota Living Heart Failure Questionnaire; KCCQ: Kansas City Cardiomyopathy Questionnaire

### Core laboratory for cardiovascular imaging

To enhance the robustness of the study for cardiovascular imaging findings, several participating centres will used specialized software to send pseudo-anonymized DICOM images to central labs for analysis. An innovative aspect of the HEAR is centralized MRI using artificial intelligence algorithms managed by the Multimodality Imaging for Research and Analysis Core Laboratory and Artificial Intelligence (MIRACL.ai) at Lariboisière University Hospital (Paris, France). This process is supervised by experts with European Association of Cardiovascular Imaging Level III certification. The MIRACL.ai will comprehensively assess each examination (including inter- and intra-observer reproducibility) and apply various post-processing techniques (such as strain analysis and artificial intelligence algorithms).

### Ethical considerations

The study will be conducted and reporting on in accordance with the principles of the Declaration of Helsinki. The HEAR is registered with the French National Agency for the Safety of Medicines and Health (*Agence nationale de sécurité du médicament et des produits de santé* (Paris, France); identifier: IDRCB 2019-A02010-57) and ClinicalTrials.gov (identifier: NCT05101304, registered on 2021–10-19). As stated above, the HEAR protocol is strictly observational. It will not modify the patient’s usual care and will not require additional consultations or examinations.

## Discussion

The European Society of Cardiology’s recently published guidelines emphasize the importance of collaboration between centres and the establishment of networks, so that patients can be referred to regional or national centres for complex diagnostic procedures and decision-making [17]. As the number of patients with CA continues to grow, we have set up the HEAR with a view to combating misdiagnosis, generating scientific and medical knowledge, improving patient care, and evaluating tools for diagnosis and for the assessment of QoL. The HEAR will also help to raise awareness of CA among healthcare professionals and to improve the care of patients with CA (especially those diagnosed recently). This multidisciplinary effort constitutes a unique opportunity to define early diagnostic findings, describe the natural history of CA, monitor patient outcomes, and improve our overall understanding of ATTR. The HEARs inputs and outputs for patients, physician and industrial partners are summarized in Fig. 3. For instance, HEAR allowed the comparison of survival outcomes in patients aged ≥80 years with cardiac transthyretin amyloidosis before and after the availability of tafamidis [18], which underscores the registry’s value as a real-world data platform for evaluating therapeutic effectiveness, patient trajectories, and healthcare strategies in CA.

